#### 2.10.2. Physical evaluation and time spent caring for a patient

Participants will be asked about physical activity type and frequency. Moreover, data regarding how long (in months) the participants have been caring for a patient (with any condition) and whether the participant performs the care for the same individual will be collected.

#### 2.10.3. Cognitive function

Cognitive function will be evaluated using the MMSE (Brucki et al., 2003), which evaluates orientation to time and place, short-term memory (recall), attention, language skills, visuospatial abilities, and ability to understand and follow instructions. The total score ranges from 0 to 30; high scores indicate greater cognitive function. In addition, the cutoff point of 25 will be used for literate individuals (Brucki et al., 2003).

### 2.11. Outcomes

Outcomes will be evaluated at the baseline, immediately after the 6-week program, and 30 days after the end of the program. A researcher not involved in the intervention will remotely reassess all participants via *Whatsapp* or *Google Meet*.

#### 2.11.1. Primary outcomes

Caregiver burden

Considering that studies have indicated a high level of burden in caregivers of individuals with ALS (de Wit et al., 2018), this outcome will be evaluated using the Zarit scale, a widely used instrument in both research and clinical practice, to assess the level of burden and stress experienced by caregivers of people with disabilities. This scale enables a quantitative assessment of perceived burden, facilitating the identification of caregivers at risk of chronic stress and exhaustion. Furthermore, it aids in planning appropriate interventions and support services for caregivers. This scale has been widely used and has an intraclass reliability coefficient of 0.88 and Cronbach's coefficient alpha of 0.77 (Taub et al., 2004). It consists of 22 questions that are scored on a 5-point Likert scale, ranging from 0 (never) to 4 (nearly always) (Al-Rawashdeh et al., 2016). The maximum score is 88 points; high scores indicate a greater level of caregiver burden (Taub et al., 2004). Moreover, the Zarit scale specifically addresses the caregiver-patient relationship and evaluates various aspects of the caregiver's life, such as physical and mental health (“Do you feel you do not have time for yourself because of the person's care?”), economic status (“Do you feel that the person's care has affected your financial wellness?”), and social wellbeing (“Do you think that your personal life was affected owing to the person's care?”).

Quality of life

The quality of life will be evaluated using the short version of the World Health Organization Quality of Life-BREF (WHOQOL-BREF) (Orley et al., 1995), which consists of 26 questions and has a Cronbach's coefficient alpha of 0.91. The first question refers to the general quality of life, and the second to satisfaction with health. The remaining 24 questions are divided into four domains: physical (e.g., “How satisfied are you with your health?”), psychological (e.g., “How often do you have negative feelings such as blue mood, despair, anxiety, depression?”), and environmental health and social relationships (e.g., “How satisfied are you with the support you receive from your friends?”). This scale specifically focuses on evaluating the caregiver-patient relationship and the physical and mental health, economic status, and social wellbeing of caregivers (Fleck et al., 2000; Vahedi, 2010) since caregivers of individuals with ALS experience a significant burden (Pagnini et al., 2010).

#### 2.11.2. Secondary outcomes

Pain

Several studies have reported that informal caregivers have an increased risk of experiencing pain, such as musculoskeletal pain and headaches (Darragh et al., 2015; Llamas-Ramos et al., 2023). Thus, the pain will be evaluated using the McGill Pain Questionnaire, a well-established tool with reasonable validity and reliability (Pimenta and Teixeira, 1996) and a Cronbach's coefficient alpha of 0.96 (Lovejoy et al., 2012). This questionnaire consists of 78 descriptors of pain, which are organized into four categories (sensory, affective, evaluative, and miscellaneous) and divided into 20 subcategories. Participants will be asked to carefully select a word from each subcategory that best represents their personal experience of pain, with an option to abstain from selecting any word if needed, e.g., in the first subcategory, the evaluated person will have the following word options: (1) vibration, (2) tremor, (3) pulsating, (4) throbbing, (5) knocking, (6) bumping (Pimenta and Teixeira, 1996).

Stress

Considering that caregiving may increase the psychological and physiological stress of the caregiver (Penning and Wu, 2016; Bidwell et al., 2021; Tough et al., 2022), stress will be evaluated using the Perceived Stress Scale (Luft et al., 2007). This scale has demonstrated good reliability and validity and a Cronbach's coefficient alpha of 0.82 (Luft et al., 2007). It comprises 14 questions, with responses scored from 0 (never) to 4 (very often), e.g., “Are you feeling nervous and stressed?”. The total score is obtained by summing all individual scores (ranging from 0 to 56); high scores indicate a greater level of perceived stress (Luft et al., 2007).

Depression

Depressive symptoms will be evaluated using the Beck Depression Inventory (Beck et al., 1961) since the caregiver burden may cause mental changes and increase the risk of depression over the years of caregiving (Gauthier et al., 2007). This widely used tool has demonstrated good reliability and validity and a Cronbach's coefficient alpha of 0.9 (Toledano-Toledano and Contreras-Valdez, 2018). It consists of 21 items evaluating various attitudes and symptoms related to depression [e.g., sadness (“I feel sad or discouraged?”), pessimism (“I feel hopeless about the future”), loss of pleasure, guilt, self-criticism, suicidal thoughts, changes in sleeping and eating patterns, fatigue, and decreased libido]. Each item is scored on a scale of 0 (indicating the absence or minimal presence of the symptom) to 3 (representing severe presence of the symptom), with higher scores indicating a higher level of depression. (Beck et al., 1961).

Nocturnal awakenings

Nocturnal awakenings will be evaluated using the *Sênior Saúde Móvel* platform (Rodrigues et al., 2022), a new wearable device to monitor outcomes related to health, such as nocturia. Nocturia is the need to wake up during sleep to urinate, with each urination preceded and followed by sleep (International Continence Society, 2018). This condition causes significant discomfort and has shown a high prevalence in adults (Vaughan and Bliwise, 2018).

Sleep patterns

Sleep patterns will also be evaluated using the *Sênior Saúde Móvel* platform (Rodrigues et al., 2022). Studies have shown that sleep disturbances are closely related to increased caregiver burden (Leggett et al., 2018; Perez et al., 2022). Moreover, hypervigilance, cohabitation with the individual being cared for, and caregiver tension have been associated with sleep impairments in caregivers. Thus, this platform will allow us to collect comprehensive data on the sleep quality and patterns of caregivers, providing valuable insights into their overall wellbeing.

Level of physical activity

The level of physical activity will be analyzed using the *Sênior Saúde Móvel* platform (Rodrigues et al., 2022) since it predicts physical and psychological stress which can impact caregivers' health (Stults-Kolehmainen and Sinha, 2014).

Heart rate variability

Considering that stress, burden, sleep disturbances, and fatigue may change the cardiovascular system, especially the heart rate, its variability can be used to screen caregivers' health. Van Der Zwan et al. (2015). Thus, the heart rate variability will be analyzed using the *Sênior Saúde Móvel* platform (Rodrigues et al., 2022).

### 2.12. Adverse events

Adverse events will be self-reported and recorded during the weekly contact with the participant during the intervention (via video or phone call), or at other periods (via message and informative booklet). However, if participants need to report any occurrence, they can contact the researchers at any moment. Potential adverse events will guide adaptations to the exercise program and help the researchers to manage difficulties faced by the caregivers.

### 2.13. Adherence rate

Adherence to the intervention will be calculated by the percentage of participants who completed the 6-week program. Moreover, adherence strategies (e.g., phone calls) will remind participants of sessions and evaluations, and schedules will be flexible and adjusted according to the needs of participants. Potential issues hampering participation or continuity in the study will be prevented or solved, such as unexplained absence in the interventions, conflicting schedules with the activities of caregivers (e.g., meals and hygiene of the individual with ALS or caregiver), and inadequate environments (e.g., noisy or lacking privacy). These issues will be solved by guiding the caregivers to perform the intervention in a calm environment (i.e., without distractions) and adjust their daily routine to spend time on health improvement and rescheduling the session days or times if needed. Two absences without replacement, illness, disorder, or persistent pain hampering continuity will be considered non-adherence to the program.

### 2.14. Statistical analysis

Data will be analyzed using the Statistical Package for the Social Sciences software version 22.0 (IBM Corp., Chicago, IL, USA). Data will be initially characterized using descriptive analysis, and the significance level will be set at 5%. The Shapiro-Wilk test will be applied to verify data normality. Differences between groups on different evaluation periods will be analyzed using linear mixed models. The Bonferroni *post hoc* may be used for statistically significant results to identify specific differences. Moreover, an intention-to-treat analysis will be used to compare the groups by including all participants as allocated after randomization, ensuring an unbiased approach. Participants' data will be analyzed based on their intervention group, regardless of any dropouts. Values from the previous evaluation will be replicated and attributed to missing data due to dropout.

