### 2.3. Power calculation

Sample size was estimated using an online calculator (Dean, 2007) based on caregiver burden (primary outcome), which was evaluated using the Zarit scale. Moreover, the effect size was calculated based on post-training data from Duran Parra et al. (2019) (mean of 16 ± 9.9 and 31.4 ± 14.9 points for experimental and control groups, respectively), with a mean difference of 15.4 between groups. Thus, 22 participants (11 per group) were estimated, and the total sample was determined as 26 participants (13 per group), considering a dropout rate of 20%.

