### 2.8. Intervention groups

#### 2.8.1. Experimental group

A physiotherapist will visit the participants of the EG face-to-face to evaluate their health, deliver the informative booklet, and instruct its use and importance. The booklet titled “Self-care program for caregivers of individuals with ALS” contains guidelines for performing physical activities at home (e.g., stretching, mobility, and strengthening) and information on healthy eating, mental health, and routine management, with a schedule for the weekly organization (Appendix 1).

Participants in EG will be divided into subgroups (three to five per subgroup). Each subgroup will participate in a 6-week self-care education program with weekly synchronous meetings (Burke et al., 2019; de Wit et al., 2019) using Google Meet or WhatsApp. Each meeting will address topics related to the physical and mental health of caregivers, including the importance of care and caregivers, physical activities to be performed at home, routine management, and healthy eating (Figure 1). A physiotherapist, psychologist, and nutritionist will lead the meetings, which will last approximately 40 min plus a maximum of 20 min to discuss whether the participants' expectations were met.

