### 2.9. Study procedures

After receiving the informative booklet, participants will respond to questionnaires to characterize the sample and evaluate cognitive function. In the baseline evaluation, the caregiver burden, quality of life, pain, stress, and depression will be evaluated. Next, participants will be randomly assigned to the CG or EG. Outcomes will be revaluated after the 6-week program (revaluation 1) and 30 days after the program (revaluation 2) (Figure 3). If the EG shows better results than CG at the end of the study, the same intervention will be available for CG to ensure equality of treatment for all participants.

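### The mixed model is described without baseline adjustment, and on either natural reading it is less precise than conditioning on the baseline score already collected

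*Protocol article*

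**What the plan says.** Section 2.14 gives the model in one sentence: "Differences between groups on different evaluation periods will be analyzed using linear mixed models". Bonferroni post hoc tests may follow a significant result. No fixed effects or covariates are named, and the role of baseline is not described. Section 2.11 lists three evaluation times: baseline, the end of the 6-week programme and 30 days later.

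Section 2.3 sizes the trial on post-training Zarit scores from an earlier study, "mean of 16 ± 9.9 and 31.4 ± 14.9 points for experimental and control groups, respectively", "with a mean difference of 15.4 between groups". It arrives at 11 per group, raised to 13 for dropout. No baseline term enters that calculation.

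On the order of events, Section 2.9 begins: "After receiving the informative booklet, participants will respond to questionnaires to characterize the sample and evaluate cognitive function". It then describes the baseline evaluation of the five questionnaire outcomes and continues: "Next, participants will be randomly assigned to the CG or EG". Section 2.8.1 puts the visit under the arm's own heading: "A physiotherapist will visit the participants of the EG face-to-face to evaluate their health, deliver the informative booklet". Section 2.8.2 has a parallel sentence for the control group.

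**The concern.** The trial has 26 participants and measures every questionnaire outcome before the programme starts. If those baseline scores predict the follow-up scores, conditioning on them removes part of the residual variance at the cost of one degree of freedom. The wording of Section 2.14 points to one of two models that do not do this:

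- baseline as a repeated response with a free mean in each arm, so that the treatment effect is a difference in change;
- a separate comparison of raw scores at each time.

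The stake is precision. Neither form is biased under randomisation.

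The second, smaller matter is sequence. Section 2.9 runs booklet, baseline, randomisation. Sections 2.8.1 and 2.8.2 describe delivery of the booklet to people already named by arm. A reader cannot be sure which order will be followed in the field.

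**Working it through.** **Reproducing the planned size.** The inputs from Section 2.3 are SDs of 9.9 and 14.9 and a difference of 15.4. Section 2.14 sets the significance level at 5%. The article gives neither sidedness nor power, so I assume two-sided and 80%.

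- Common SD = √((9.9² + 14.9²)/2) = √160.01 = 12.65; standardised difference = 15.4/12.65 = 1.22.
- n per group = 2 × 160.01 × (1.960 + 0.842)² / 15.4² = 10.59, so 11 per group and 22 in total. This matches the article. At 90% power it would be 15 per group.

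The planned size therefore corresponds to a comparison of post-scores that makes no use of baseline.

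**Variance of the three contrasts.** Let ρ be the correlation between baseline and follow-up, and assume the same SD at both times. In units of the post-score variance:

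- post-score comparison: 1
- change from baseline (group-by-time): 2(1 − ρ)
- baseline as covariate, or common baseline mean: 1 − ρ²

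Relative to adjustment, the post-score form is 1/(1 − ρ²) times as variable and the change form 2/(1 + ρ) times. The power columns use the noncentral t with 11 per group and 15.4 points (20 degrees of freedom, or 19 with the covariate).

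| ρ (assumed) | post ÷ adjusted | change ÷ adjusted | power, post | power, change | power, adjusted |
|---|---|---|---|---|---|
| 0.3 | 1.10 | 1.54 | 77.5% | 63.2% | 81.0% |
| 0.5 | 1.33 | 1.33 | 77.5% | 77.5% | 87.8% |
| 0.7 | 1.96 | 1.18 | 77.5% | 93.9% | 96.6% |
| 0.8 | 2.78 | 1.11 | 77.5% | 99.0% | 99.5% |

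For half the planned difference (7.7 points) at ρ = 0.5, power is 27.5% under either unadjusted form and 34.7% with adjustment.

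**Small-sample correction.** The factor 1 − ρ² is a large-sample value. Estimating the slope and absorbing chance imbalance multiplies the adjusted variance by about 1 + 1/(2n − 4) = 1 + 1/18 = 1.056 at n = 11. At ρ = 0.5 the advantage becomes 1.33/1.056 = 1.26. The adjusted standard error becomes 12.65 × √0.75 × √(2/11) × √1.056 = 4.80, and 15.4/4.80 = 3.21 on 19 degrees of freedom gives power of about 86%. At ρ = 0.3 the advantage over a post-score comparison shrinks to 1.10/1.056 = 1.04.

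**Booklet before baseline.** I simulated 5,000 trials of 11 per group at ρ = 0.5, with a booklet effect that varied between people and lowered the baseline score by 5 points on average in both arms. The true difference was −15.4. Post-score, change and covariate-adjusted estimates all averaged about −15.5. The SD of the adjusted estimate was 4.83, against 4.77 with no booklet effect. A shift common to both arms before randomisation therefore leaves the contrast unbiased and costs almost nothing in precision.

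**The case against.** The strongest reply is that Section 2.14 is silent on adjustment and does not exclude it. A journal article can leave model terms to an analysis plan, and nothing it says rules out a baseline covariate or a constrained baseline mean. That stands against any claim that the trial will not adjust. It does not remove the point. The sentence describes comparisons at the evaluation times, baseline is one of them, and the ordinary reading is one of two forms that both use the data less well.

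A second reply is that the trial was sized without baseline, so adjustment improves on the plan and does not repair an error. That is correct. The size of the gain also rests on a correlation the article does not give.

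Two stronger readings are tempting, and the article supports neither.

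- **Chance imbalance as bias.** With the SD of 12.65 borrowed from post-training scores, the standard error of the baseline difference is 12.65 × √(2/13) = 4.96, so a gap of 5 points or more arises in about 31% of trials. That says only that a normal variable exceeds about one standard error roughly a third of the time. Under randomisation such gaps add variance; they do not bias the estimator.
- **A baseline spoiled by the booklet or by known allocation.** Section 2.9 puts randomisation after baseline. Section 2.7 withholds the envelope contents from the professionals until the programme starts. Both arms receive the same booklet, and the trial's question is synchronous against asynchronous follow-up. On that order the baseline is a valid covariate, and only within-arm change loses a pre-booklet reference. Sections 2.8.1 and 2.8.2 describe each arm's package without fixing its timing. The simulation would not cover a baseline taken with allocation known, which is why the wording still needs aligning.

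**Conclusion.** The point holds as a recommendation on precision. The model as worded does not state baseline adjustment, and either natural reading is less efficient than conditioning on the baseline score. The large-sample variance penalty is 1.10 to 2.78 for a post-score comparison and 1.54 to 1.11 for a change contrast over ρ from 0.3 to 0.8. At ρ = 0.5 the gain is from about 78% power to between 86% and 88%. At low correlation the gain over post-scores is slight, and at high correlation the gain over change scores is slight.

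These figures assume equal SDs at the two times, 11 complete participants per group and a two-sided 5% test. They ignore the rule in Section 2.14 that replicates the previous value for dropouts.

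The inconsistency over booklet timing is a minor wording matter and does not threaten the between-arm comparison on Section 2.9's order.

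**What to change.** In Section 2.14, or in the analysis plan, specify the model for Zarit, WHOQOL-BREF and the other questionnaire scales: a linear mixed model of the scores at revaluations 1 and 2, with group, time, group-by-time and the baseline score of that scale as covariate. An alternative is to keep baseline as a response and constrain its mean to be equal in the two arms. The cost is a sentence of text and one degree of freedom, with no new data.

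Separately, align Sections 2.8.1 and 2.8.2 with Section 2.9 on when the booklet is delivered. Confirm that the baseline questionnaires are completed before allocation. If within-arm change is to be reported, confirm that they also precede the booklet. This needs clearer wording and, at most, a change in the order of steps around the first visit.

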#### 2.8.2. Control group

A physiotherapist will also visit the participants in the CG to evaluate their health condition, deliver the informative booklet, and instruct them on the importance of reading and using the booklet (Appendix 1). Next, trained researchers will contact the participants via phone calls during the 2nd to 6th week of the intervention to verify their physical and mental health and collect information on completing physical exercises and habits proposed in the booklet. The researcher should record any relevant information. Figure 2 shows the questions for participants. After the intervention period, a new visit will be performed for revaluation.

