## 3. Discussion

This is the first study comparing a synchronous (follow-up via video call) and asynchronous (follow-up via messages and informative booklet) multidisciplinary self-care educational program for caregivers of individuals with ALS. According to Chi and Demiris (2015), caregivers approve and feel comfortable using telerehabilitation to improve self-care and quality of life. In this sense, telerehabilitation has been growing in the healthcare field and can be a useful tool to promote physical activities and self-care.

Despite being aware of the benefits of physical activity, caregivers face barriers, such as lack of support from family members, self-motivation, and time to perform self-care activities, guilty feelings, and stress (Farran et al., 2008; Marquez et al., 2012; Martin and Keats, 2014). Most caregivers have reported difficulty performing self-care activities because they prioritize patient care (Son et al., 2007; Farran et al., 2008; Snyder and Vitaliano, 2020). In this sense, these barriers will be addressed in this multidisciplinary study, highlighting the need for interventions involving different professionals (e.g., psychologists, and nutritionists) for the biopsychosocial management of caregivers. Telerehabilitation aims to facilitate adherence to this program.

In this study, all participants will receive the informative booklet on health and self-care from a multidisciplinary team, allowing easy access to this information. This study aims to understand whether monitoring and providing synchronous information result in better outcomes than asynchronous information. It may contribute to the knowledge about the applicability of telerehabilitation for caregivers of individuals with ALS and reinforce the need for self-care.

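### Absence from the program is listed as an exclusion criterion although it can only occur after randomisation, which conflicts with the promised intention-to-treat analysis

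*Protocol article*

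**What the plan says.** Four parts of the protocol article bear on the point.

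- **2.14 Statistical analysis:** "an intention-to-treat analysis will be used to compare the groups by including all participants as allocated after randomization". It adds: "Participants' data will be analyzed based on their intervention group, regardless of any dropouts". On gaps in the data: "Values from the previous evaluation will be replicated and attributed to missing data due to dropout".
- **2.6.2 Exclusion criteria:** the last item is missing the program on at least two days in a row with no make-up. The other items (health conditions, early pregnancy, psychiatric medication) can be established before randomisation.
- **2.13 Adherence rate:** "Two absences without replacement, illness, disorder, or persistent pain hampering continuity will be considered non-adherence to the program".
- **2.9 Study procedures:** after the baseline evaluation, "Next, participants will be randomly assigned to the CG or EG". The six-week program follows.

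The arms differ in what can be missed. For the EG (2.8.1): "Each subgroup will participate in a 6-week self-care education program with weekly synchronous meetings". For the control group, CG (2.8.2): "trained researchers will contact the participants via phone calls during the 2nd to 6th week of the intervention".

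**The concern.** An exclusion criterion ordinarily means that the person is not in the trial. A caregiver cannot be absent from a program that has not started, so this item can act only on people already randomised. The same caregiver may then be excluded under 2.6.2, a non-adherer under 2.13, and a full member of the analysis under 2.14. The rule in 2.14 speaks of dropouts. It does not say what happens to someone whom the investigators exclude.

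Two harms are possible. If exclusion means removal from the analysis, the randomised comparison is lost for those caregivers, and the loss is likely to be uneven between arms. If it means only that follow-up stops, outcomes go missing for people who could still be reassessed, and 2.14 fills the gaps with carried-forward values. With 13 per arm, two or three caregivers are 15% or 23% of the EG (2/13, 3/13).

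**Working it through.** **1. Order of events.** Section 2.9 gives baseline, then random assignment, then the program. The absence item in 2.6.2 is therefore a post-randomisation event.

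**2. Which arm.** Meetings that can be missed and replaced are described only for the EG. The CG has a booklet and calls made by researchers. The criterion names no arm, so removal mainly from the EG is an inference.

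**3. Link to burden.** Section 2.13 names clashes with caregiving tasks as an obstacle to participation, and section 3 expects follow-up of the EG subgroups to be difficult because of caregivers' demands. Neither gives a relation to the Zarit score, so the correlation below is an assumption.

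**4. The plan's own figure (2.3).** Pooled SD = √[(9.9² + 14.9²)/2] = 12.65. With a difference of 15.4, two-sided 5% and 80% power (neither sidedness nor power is stated; both are assumed), n = 2 × (1.96 + 0.842)² × 12.65²/15.4² = 10.6, so 11 per group and 22 in all, as stated. Removing 3 EG caregivers lowers t-test power from 0.846 (13 v 13) to 0.788 (10 v 13). The power loss is modest; the issue is bias.

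**5. Illustration of bias.** Assumptions: no true effect; SD 14.9 (the planning control value in 2.3); 13 per arm; the 3 EG caregivers most prone to absence are removed; correlation ρ between that tendency and burden. The figure of 3 borrows the 20% dropout allowance (13 × 0.20 = 2.6), which is not an absence rate.

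The three largest of 13 standard normal values average 1.668, 1.164 and 0.849, a sum of 3.68. The 10 who remain therefore average −3.68/10 = −0.368 on the absence scale.

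- *Post-program scores:* bias = ρ × 14.9 × 0.368, which is 1.6 / 2.7 / 3.8 points for ρ = 0.3 / 0.5 / 0.7. Simulation agrees. The chance of falsely finding the EG better rises from 2.5% to 4.3% / 6.5% / 9.3%.
- *Baseline-adjusted* (assumed baseline–post correlation 0.7; absence equally related to burden at both visits): roughly (1 − 0.7) times the above, or 0.5 / 0.8 / 1.2. Simulation gives 0.5 / 0.9 / 1.3, and a false-benefit rate between about 3% and 5%.
- *Change from baseline*, same assumption: the shift is equal at both visits and cancels, so the bias is about 0 and the false-benefit rate about 2.5%.
- *Change from baseline, if absence tracks worsening burden:* SD of change = 14.9 × √[2(1 − 0.7)] = 11.5, so bias = ρ × 11.5 × 0.368 = 1.3 / 2.1 / 3.0 points.
- *ρ = 0:* no bias in any of these.

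**The case against.** The strongest reply is that 2.14 already settles the matter. It includes everyone as allocated, regardless of dropout, and no section says that an absent caregiver's data leave the analysis. On that reading, 2.6.2 ends participation in the program, 2.13 labels it, and 2.14 keeps the person in. This reading is workable, so a reader who infers that the three sections cannot possibly be followed together goes too far. The article does not state it, however, and the ordinary meaning of an exclusion criterion points the other way.

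Other stronger inferences also fail:

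- *That exclusion can occur only in the EG.* The criterion names no arm, and section 3 describes both arms as forms of one educational program, so a missed CG call could be argued to count.
- *That the article shows more burdened caregivers skip remote sessions.* The introduction says that care demands hamper face-to-face programs and offers remote delivery as the answer. The statement in section 3 that "Most caregivers have reported difficulty performing self-care activities because they prioritize patient care" concerns self-care, not attendance. Sections 2.13 and 3 (on caregivers' demands) are closer, but 2.13 also plans reminders and rescheduling.
- *That the false-positive rate reaches 9.3%, or the bias 25% of the planned 15.4 points (3.8/15.4).* Those figures belong to a comparison of post-program scores alone. Section 2.14 plans linear mixed models over the evaluation periods, and burden is measured at baseline. Selection on burden level shrinks or cancels once baseline enters.

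Finally, the trigger counts consecutive days while meetings are weekly, so read literally it might rarely fire. That makes the size less certain but does not remove the conflict.

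**Conclusion.** The concern stands as an unreconciled conflict: an event that can only follow randomisation is listed as an exclusion criterion in a trial that promises to analyse everyone as allocated. Applied as written, 2.6.2 would break that promise.

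The direction of any bias, towards the EG, is plausible but not established. It rests on removals falling mainly in the EG and on absence being related to burden. The size is unknown: in the illustration it runs from about 0 to 3.8 points, depending on the correlation, on how baseline enters the model, and on whether absence tracks the level of burden or its worsening. Because 2.14 does commit to all randomised participants and a lenient reading exists, this should be fixed, but the documents do not show that the primary comparison is already compromised.

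**What to change.** - Delete the absence item from 2.6.2, so that exclusion rests only on facts known before randomisation.
- State in 2.13 and 2.14 that caregivers who miss sessions are recorded as non-adherent, are still reassessed at revaluations 1 and 2 by the remote route that 2.11 provides for all participants, and are analysed in the arm to which they were allocated.
- If an analysis without them is wanted, label it a supplementary per-protocol analysis that cannot replace the primary result.

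The cost is one deleted item and one or two sentences by amendment, plus a few remote reassessments of non-attenders. The planned sample size of 26 does not change. The estimate may be slightly less favourable to the program because non-attenders are kept.
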